Adverse events: the proportion of participants exhibiting adverse events of any grade as defined using the DAIDS Table for Grading the Severity of Adverse Events, at 7, 14, 35, and 90 days [28].Symptomatic microbiologically confirmed SARS-CoV-2 infection: proportion of participants with fever, cough, or other respiratory/systemic symptoms (including but not limited to fatigue, myalgias, arthralgias, shortness of breath, sore throat, headache, chills, coryza, nausea, vomiting, diarrhea), combined with microbiologic confirmation of SARS-CoV-2 infection by PCR, by day 14.Seropositivity: proportion of participants with reactive serology at day 35.Days of hospitalization attributable to COVID-19 disease: The median number of days (or partial days) spent admitted to an acute care hospital will be tabulated both at day 35 and day 90.Respiratory failure requiring ventilatory support attributable to COVID-19 disease: The median number of days (or partial days) requiring (i) non-invasive or (ii) invasive ventilation will be tabulated both at day 35 and day 90.Mortality (proportion of participants who die) attributable to COVID-19 disease and all-cause mortality will be tabulated at 35 and 90 days.Short-term psychological impact of exposure to COVID-19 will be measured at day 14 using the K10, a validated measure of non-specific psychological distress, with results aggregated as the proportion with a score of ≥ 16 [45, 46].Long-term psychological impact of exposure to COVID-19 will be measured at day 90 using the Impact of Event Scale, a validated measure of traumatic stress response, with results aggregated as the proportion with a score of ≥ 26 [47, 48].Health-related quality of life will be measured using the EQ-5D-5L (EuroQol-5D) (https://euroqol.org/eq-5d-instruments/eq-5d-5l-about/). The EQ-5D consists of two pages: the EQ-5D descriptive system and the EQ visual analog scale (EQ VAS). The descriptive system comprises five dimensions: mobility, self-care, usual activities, pain/discomfort and anxiety/depression. The tool will be administered to participants at 1, 14, 35 and 90 days; the primary interest is in the median index value at 14 days.

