### Sample size {14}

Our target sample size is 244 rings, assuming an average ring size of 5 individuals (i.e., a total of *n* = 1220 participants), an intra-class correlation coefficient (ICC) of 0.05 [31], a secondary attack rate (proportion of those exposed who get infected, p_0_) of 15%, and inflation for 10% loss-to-follow-up. This sample size will allow us to detect whether the study drug decreases the relative risk of COVID-19 by at least 40% (effect size estimated in the MERS-CoV LPV/r PEP study [8]), with 80% power and alpha = 0.05.

The number of contacts per case may vary considerably but was estimated at 5 based on published data for SARS in Beijing (mean = 3.8) [49]. We considered ICC values of 0.02 and 0.05 [31]. The estimated secondary attack rate of 15% was originally estimated based on transmission rates for SARS [49–52] and influenza [53–56] and is corroborated by recent studies on COVID-19. Among 19 household contacts of the first 10 patients with travel-related COVID-19 in the United States, *p*_0_ = 10.5% (95%CI = 2.9%–31.4%) [57]. In Shenzhen, the secondary attack rate among 686 household contacts was 11.2% (95%CI = 9.1–13.8) [58]. In Guangzhou, it was 19.3% (95%CI = 15.5–23.9%) among household contacts sharing a residential address with a case [59]. Investigators in Wuhan found secondary transmission in 64/392 household contacts (16.3%) [60]. Illness compatible with COVID-19 developed in 58/407 (14.8%) of placebo arm participants in a recent trial of hydroxychloroquine as COVID-19 PEP [61].

The parameters *p*_0_, ICC and cluster size are important drivers of statistical power [62, 63], but are still being elucidated for COVID-19 and may vary according to context. We will thus apply an adaptive trial design [63] to revise our sample size calculations based on day 14 data from the first 60 clusters.

Another interim analysis will be done when day 14 data for 50% of the target sample have accrued; our independent data safety monitoring committee will advise on trial continuation/switching to a different agent, taking external data into account, and through additional confidential consultation with the WHO Core DSMC on COVID-19 prophylaxis, with which we are linked [5].

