### Concealment mechanism {16b}

Randomization will be implemented using a secure interactive web-based response system (Research Electronic Data Capture, REDCap). To ensure allocation concealment, the randomization sequence is fully concealed, and treatment assignment will not be revealed until the moment of randomization. Study personnel will then notify participants about their assigned study arm at the time of the baseline visit.

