## Statistical methods

### Statistical methods for primary and secondary outcomes {20a}

The primary outcome is microbiologically confirmed SARS-CoV-2 infection, i.e., detection of viral RNA in a respiratory specimen (oropharyngeal/nasal swab, nasopharyngeal swab, sputum specimen, saliva specimen, oral swab, endotracheal aspirate, bronchoalveolar lavage specimen) by day 14. Our primary analysis will be a generalized linear mixed model (GLMM) with logit link to estimate the effect of LPV/r on the probability of infection while accounting for clustering of participants in rings, with stratification by the randomizing site. The primary analysis will be unadjusted; in addition, multivariable models will adjust for key characteristics of both contacts (age, sex, co-morbidity, exposure characteristics such as type, duration, and timing) and index cases (illness severity, concomitant medications, etc.). In particular, we will include sex/gender-based analyses with variables specific to contacts and types of exposures. Participants with specimens positive for SARS-CoV-2 at baseline will be permitted to continue in the trial and follow all study procedures, including completion of the 14-day course of study drug for those in the active arm, as noted in section 12.2.2. These participants will be excluded from the primary and secondary analyses regarding LPV/r as PEP, but included in secondary analyses regarding early LPV/r treatment, as noted below.

To assess safety, adverse events will be tabulated according to grade and causality assessment using definitions from the DAIDS Table for Grading the Severity of Adverse Events [28], and compared between study arms.

As for the primary analysis outlined above, GLMM with logit link (for dichotomous outcomes) or identity link (for continuous outcomes) will also be used to compare the following secondary outcomes between study arms:

Symptomatic COVID-19 disease by day 14Seropositivity by day 35Days of hospitalization attributable to COVID-19 disease by day 90Respiratory failure attributable to COVID-19 disease requiring (i) non-invasive and (ii) invasive ventilation by day 90Mortality attributable to COVID-19 diseaseShort-term psychological distress, defined as scoring ≥ 16 on the K10 [45, 46] at day 14Long-term traumatic stress response, defined as scoring ≥ 26 on the IES scale [47, 48] at day 90Health-related quality of life, measured by the EQ-5D-5 L on days 1, 14, 35, and 90

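### The K10 and Impact of Event Scale models name no baseline distress covariate; the day-1 EQ-5D-5L anxiety/depression item could serve, but only if it is answered before the arm is disclosed

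*Protocol article*

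**What the plan says.** Short- and long-term psychological distress are separate items in the list of secondary objectives (Objectives). Under Outcomes, "Short-term psychological impact of exposure to COVID-19 will be measured at day 14 using the K10, a validated measure of non-specific psychological distress", with results given as the proportion scoring 16 or more. The Impact of Event Scale is measured at day 90 and reported as the proportion scoring 26 or more. Neither instrument is scheduled at baseline in the article.

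The same section describes the EQ-5D-5L, whose dimensions are "mobility, self-care, usual activities, pain/discomfort and anxiety/depression". On timing: "The tool will be administered to participants at 1, 14, 35 and 90 days". The article uses it only for the quality-of-life outcome and general health-economic scoring.

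The statistical methods section states: "As for the primary analysis outlined above, GLMM with logit link (for dichotomous outcomes"), and it lists both distress outcomes under that sentence. The primary analysis is declared unadjusted. Additional multivariable models use age, sex, co-morbidity and exposure characteristics of contacts, and features of index cases. No distress variable is named.

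On order of events, footnote a of Table 1 places the baseline activities after the cluster has been randomised. The Concealment mechanism section says: "Study personnel will then notify participants about their assigned study arm at the time of the baseline visit". The trial is open-label. Whether the day-1 questionnaire comes before or after disclosure is not stated.

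**The concern.** How distressed a person is at entry is usually a good predictor of how distressed that person is two weeks or three months later. An analysis that ignores it carries more residual variation than necessary and leaves a chance imbalance in baseline distress uncorrected. Here a related item is already scheduled on day 1, and the article states its model and covariate list without using it.

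At stake is some power, and protection against chance imbalance, for two secondary objectives. There is a second risk: if the item were adopted as a covariate without fixing when it is answered, relief or worry about the allocation could already be in the answer, and adjustment would then remove part of the arm difference it is meant to sharpen.

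**Working it through.** **1. The plan's own figure.** It concerns the primary outcome only. Inputs from the Sample size section: "a secondary attack rate (proportion of those exposed who get infected, p_0_) of 15"%; a drug that "decreases the relative risk of COVID-19 by at least 40"%, so 15% against 9%; "with 80% power and alpha = 0.05"; rings of 5; ICC 0.05.

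- Per arm, independent: [1.960·√(2·0.12·0.88) + 0.842·√(0.15·0.85 + 0.09·0.91)]² / 0.06² = 460.
- Design effect 1 + (5 − 1)·0.05 = 1.20. Clusters per arm: 460·1.20/5 = 110.4 (plan: 110).
- Rings after 10% loss: 220/0.9 = 244.4 (plan: 244).

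The figure reproduces, and this point does not touch it. No power is stated for K10 or the Impact of Event Scale.

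**2. Gain from a clean covariate.** Everything in this step is assumed, because the documents give no distress prevalence, effect or correlation. A normally distributed latent baseline is cut into five levels (cumulative 55, 82, 95 and 99%). It is correlated with a latent later score, of which 20–40% lies above the cut-off. R² is the share of outcome variance explained by the item. If d is the unadjusted effect divided by its standard error, power with the item is about Φ(d/√(1 − R²) − 1.960).

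Three starting points were used: 80%, 50%, and the power for an illustrative 0.2 SD shift. For the last:

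- Effective number per arm: 550/1.20 = 458.
- Control proportion 0.35; active Φ(Φ⁻¹(0.35) − 0.2) = 0.279; difference 0.0708.
- Standard error √[(0.35·0.65 + 0.279·0.721)/458] = 0.0306, so d = 2.315 and power is Φ(0.355) = 63.9%.
- With R² = 0.13: 2.315/√0.87 = 2.482, and Φ(0.522) = 69.9%.

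| Latent correlation | R² | from 80% | from 63.9% | from 50% |
|---|---|---|---|---|
| 0.2 | 0.02 | 80.8% | 64.8% | 50.8% |
| 0.3 | 0.04 | 81.6% | 65.7% | 51.6% |
| 0.4 | 0.08 | 83.2% | 67.5% | 53.3% |
| 0.5 | 0.13 | 85.2% | 69.9% | 55.6% |
| 0.6 | 0.19 | 87.6% | 73.0% | 58.6% |

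The gain runs from about 1 point to about 8, and reaches 9 in the corner cases. Simulated logistic models with 458 per arm agree with the middle column to within about a point, and rejection stays near 5% when there is no effect.

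**3. If the true shift is small.** The design effect on infection is 15 − 9 = 6 percentage points. If infection raised distress by a full SD (assumed), the arm shift through infection is 0.06·1 = 0.06 SD. At 458 per arm, power is then 10.8% without the item and 10.9% to 12.2% with it, a gain of 0.1 to 1.4 points.

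**4. If the item is answered after disclosure.** Suppose knowing the arm shifts the day-1 item by 0.1 to 0.3 SD (assumed) and that shift carries through to the later score. For a shift of 0.2 SD and correlation 0.5, the risk difference is −0.0346 unadjusted and −0.0072 adjusted, so 1 − 0.0072/0.0346 = 79% of that component is removed. Across shifts of 0.1 to 0.3 SD and correlations of 0.3 to 0.6, the share removed is 75% to 86%.

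**The case against.** The strongest reply is that the article's schedule does not supply a clean baseline. Day-1 activities follow randomisation, and participants learn their arm at the same visit, so the unadjusted comparison is the safe default. This stands, and it is why the point is conditional on the order of tasks. It does not remove the point, because the order can be fixed.

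A second reply is that covariate choice belongs to the analysis plan or full protocol, neither of which is shown, and that the listed co-morbidity could include prior mental illness. This stands in part: one can say only that no explicit distress measure is named. But the article does state the model, call it unadjusted and list covariates, so its text can be commented on.

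Third, the effect could be too small for any covariate to matter (step 3), and the numbers analysed will be lower than 550 per arm because participants positive at baseline are excluded. Both stand.

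A reader might infer that everyone supplies a baseline measure of much the same construct, so that power is being given up for nothing. The documents do not support that. Enrolment starts at 6 months of age, and guardians may complete questionnaires with minors. The Impact of Event Scale measures response to a stressful event, which one generic item may predict weakly. And the item costs nothing only if it is answered before disclosure.

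**Conclusion.** The point holds as a minor improvement. Neither distress comparison has a named baseline distress covariate, and an item that could serve is already scheduled on day 1. It can be used safely only if answered before the arm is known. The expected gain is about 1 to 8 points of power (at most 9) under assumed correlations of 0.2 to 0.6 and a 0.2 SD shift, with the lower end more likely for the Impact of Event Scale. It is close to nil if the true shift is very small. None of these inputs comes from the documents, so the figures show a range and do not measure the loss in this trial.

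It would be wrong to conclude that the planned unadjusted comparison is biased or invalid, or that the primary outcome or its sample size is affected.

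**What to change.** - State that the day-1 EQ-5D is completed before the arm is disclosed, in the same way in both arms and for video, telephone, paper and interview completion, and record the order. This also protects the day-1 value as a baseline for the quality-of-life outcome.
- Name the day-1 anxiety/depression level as a covariate in the K10 model and, with less gain expected, in the Impact of Event Scale model. Keep the unadjusted result alongside, since in a logit model the adjusted odds ratio is conditional on the item and not directly comparable with the unadjusted one.
- Where completion before disclosure cannot be verified, including for participants already enrolled, treat the item as missing (a missing category) or rely on the unadjusted result.

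Cost: a fixed task order at an existing visit, one extra covariate in two models, and a rule for missing items. There is no new instrument, visit or participant. The item will be of limited use for young children whose questionnaires are completed with guardians.

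### Quality of life is defined as the median EQ-5D-5L index at day 14, but the planned identity-link model estimates a difference in means, and the role of the day-1 score is left open

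*Protocol article*

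**What the plan says.** In the protocol article, Outcomes {12} gives the EQ-5D-5L schedule first: "The tool will be administered to participants at 1, 14, 35 and 90 days". It then sets the target: "the primary interest is in the median index value at 14 days". The same entry explains that the instrument has a descriptive system and a visual analog scale, so naming the index is a deliberate choice.

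Statistical methods for primary and secondary outcomes {20a} carries the primary analysis over to a list of secondary outcomes. For those that are continuous, the model has an "identity link (for continuous outcomes"). The section also states the purpose of the model, which "will also be used to compare the following secondary outcomes between study arms". Quality of life is the last item in that list, given as the EQ-5D-5L on days 1, 14, 35 and 90. The item mentions no median, no priority for day 14, no choice between index and visual analog scale, and no role for the day-1 score.

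On adjustment, the same section says "The primary analysis will be unadjusted; in addition, multivariable models will adjust for key characteristics of both contacts" and index cases. The covariates it names do not include a baseline quality-of-life score.

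On timing, the schedule of events puts cluster randomization at screening, before the baseline activities. Concealment mechanism {16b} adds: "Study personnel will then notify participants about their assigned study arm at the time of the baseline visit".

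**The concern.** A pre-specified outcome needs a summary measure, a time point and an analysis that estimates that summary at that time point. Here the summary measure and the analysis do not match. A reader of the Outcomes section expects a comparison of medians. A reader of the methods section expects a difference in means.

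The difference can matter for this instrument. The index has an upper limit, and exposed contacts who are mostly well may cluster at or near it. A median can then be equal in both arms while the means differ, and the reverse can also happen. In an open-label trial, leaving two summaries and four days available allows the choice to be made after results are seen.

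There is also a missed opportunity. The day-1 index is already collected and is the natural covariate for the day-14 index, yet the model is described as following an unadjusted primary analysis.

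**Working it through.** **No plan figure to reproduce.** The article gives no standard deviation, effect size or power for the EQ-5D-5L. Its sample size, "with 80% power and alpha = 0.05", rests on the PCR outcome alone, and none of its inputs concern quality of life.

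**Step 1: the two sections side by side.**

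| Element | Outcomes {12} | Statistical methods {20a} |
|---|---|---|
| Score | Index | Not named |
| Summary | Median | Mean (identity link) |
| Time point of main interest | Day 14 | Four days listed, none singled out |
| Use of day 1 | Administration day only | In the list, role not stated |

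The summary row is a conflict. The other rows are matters that the methods section does not carry over or leaves open.

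**Step 2: can mean and median disagree?** This is an illustration on assumed data, because the article gives no score distribution. Let a share f of an arm score below the ceiling of 1, with losses following a Beta(2, 8) distribution, whose mean is 2/(2 + 8) = 0.2. The arms have shares f_C and f_T.

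- Difference in means = −(f_T − f_C) × 0.2.
- The median of an arm stays at 1 while f is below 50%.

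| f_C | f_T | Difference in means | Difference in medians |
|---|---|---|---|
| 30% | 40% | −0.10 × 0.2 = −0.020 | 0 |
| 30% | 48% | −0.18 × 0.2 = −0.036 | 0 |
| 48% | 52% | −0.04 × 0.2 = −0.008 | −0.036 |

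In the third row, the median of the second arm falls at the (0.52 − 0.50)/0.52 = 3.8% point of the losses, which is about 0.036. A simulation with one million values per arm gave the same figures. In the first two rows the median shows nothing where the mean shows a difference. In the third the median exaggerates a very small shift.

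**Step 3: what would the day-1 index add as a covariate?** With correlation ρ between the day-1 and day-14 index, adjustment multiplies the residual variance by 1 − ρ². The range for ρ is assumed.

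- ρ = 0.5: 1 − 0.25 = 0.75, a cut of 25%.
- ρ = 0.7: 1 − 0.49 = 0.51, a cut of 49%.

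The gain is smaller if clustering or ceiling effects weaken the correlation.

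**The case against.** The strongest reply is that only the median-versus-mean mismatch is in the text. The four days in the methods section can be read as a repeat of the administration schedule, with the day-14 priority from the Outcomes section still in force. That reply is right, and it limits the point in three ways.

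- **Time point.** A reader might infer a contradiction between day 14 and four visits. The article does not establish one. Other items in the same list do name a single analysis day (the K10 at day 14, the Impact of Event Scale at day 90), which makes the four-day entry look like an analysis set. That is suggestive only.
- **Dilution.** A reader might infer that one arm effect is pooled over all four visits, so that a day-14 effect is diluted. The article does not write out the model. Separate day-specific comparisons or an arm-by-visit model fit the wording equally well, so no dilution figure should be attached to this plan.
- **Day 1 as an outcome.** A reader might infer that the day-1 score is compared between arms as if it could show a drug effect. The list permits that reading but does not state it, and a longitudinal model can validly hold the baseline in the response if the arms are constrained to be equal there.

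It can also be said that an unadjusted comparison is valid in a randomized trial, that covariate detail is often left to an analysis plan, and that a median is a defensible choice for a score with a ceiling. All three are fair. The covariate is therefore an efficiency gain and not the correction of an error, and the fix should not insist on the mean. None of these replies makes an identity-link model estimate a difference in medians.

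**Conclusion.** The point holds as a mismatch between two sections: the named quantity is a median, and the stated model estimates a mean. It does not depend on how the day list is read, since a day-14 contrast from any version of that model is still a difference in means. The unspecified role of day 1 is a secondary matter.

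The possible disagreement between the summaries rests on an assumed pile-up of scores at the ceiling. The precision gain rests on the assumed correlation and on day 1 being a clean baseline, which the article does not secure: it places disclosure of the arm at the same visit and gives no order of tasks.

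This is a minor point on one secondary outcome. It deserves a wording change because the repair is nearly free.

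**What to change.** State one day-14 summary of the EQ-5D-5L index in both Outcomes {12} and Statistical methods {20a}, with an analysis that estimates it and respects the rings.

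- **Simplest choice, keeping the planned model:** the between-arm difference in mean index at day 14, from the site-stratified mixed model with ring as random effect and the day-1 index as covariate. Report days 35 and 90 as separate visit-specific contrasts, and the median as description.
- **If the median is kept:** name a cluster-aware method for comparing medians and drop the identity-link model for this outcome.
- **Baseline visit:** have the EQ-5D-5L completed before the participant is told the arm. A self-reported score given after disclosure in an open-label trial is not a clean baseline. Recruitment has already opened, so where the order cannot be shown for scores already collected, give the unadjusted day-14 contrast alongside.

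The cost is wording in two sections and the order of tasks at one visit. No new data are needed.
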